### Blood pressure measurement

Blood pressure will be measured for all >
20-year-old participants and pregnant women during each step. Research staff will use an Omron HEM-907 blood pressure device, which is comparable to the gold standard mercury sphygmomanometers in terms of measurement and meets the Association for the Advancement of Medical Instrumentation’s criteria.^89^ Blood pressure will be measured following the guidelines described by Pickering *et al* and Giorgini *et al*.^90 91^ Caffeine (tea, coffee, carbonated beverages), eating, heavy physical activities and smoking will be proscribed for 30 min prior to measuring blood pressure. Participants will rest for 5 min sitting on a chair keeping their arm supported. An appropriate size cuff and calibrated instrument will be used for different age groups and the blood pressure instrument will be positioned at heart level. Blood pressure will be measured three times; first left arm, then right arm, then again left arm. Both systolic and diastolic blood pressures will be recorded from all measurements. The arithmetic mean of three systolic blood pressure measurements will be used as the primary outcome. However, if a systolic blood pressure measurement differs by 10% from the other measurements, that measurement will be excluded when calculating the arithmetic mean systolic blood pressure.

### Biomarker measurements

Field research staff will instruct the participants to collect 24 hours urine sample during each household visit. The volume of the urine samples will be noted at household level, and a sample of 25 mL urine will be collected and transported to the field laboratory at 2–8°C within 6 hours of collection for processing, analysis and storage. Aliquots of each participant’s urine sample will be made for biochemical and electrolyte measurements. Urinary creatinine concentration will be measured by a colorimetric method (Jaffe reaction) using a semiauto biochemistry analyser (Evolution 3000, BSI, Italy). Urinary total protein will be estimated using a light sensitive coloured reagent (Randox, UK). We will use the direct ion selective electrode method for urinary sodium measurements using a semiauto electrolyte analyser (Biolyte2000, Bio-care, Taiwan). We will measure the uric acid concentration in blood by an enzymatic colorimetric method (Evolution 3000, BSI). We will perform routine quality control for all tests using standard quality control reagents (Bio-Rad Laboratories, USA) and 5% of samples will be cross-checked at the International Centre for Diarrhoeal Disease Research, Bangladesh (icddr,b) central laboratory in Dhaka.

### Data management and monitoring

The data collection instrument will be programmed and field research staff will use handheld computers to collect data. Appropriate range values and data values will be programmed to minimise data entry errors. The data set downloaded from handheld devices will be cleaned and checked by the site investigators. All laboratory data will be double entered. Data will be stored in icddr,b’s data repository system, in compliance with the system’s requirements and will be publicly available after analysing the primary result.

The research staff will be trained for identifying adverse events such as hypertension and hypertensive disorders in pregnancy. They will report to the investigators following identification of these patients and the investigators will assess whether these adverse events need to be reported to icddr,b's Ethical Review Committee.

### Statistical methods

We will conduct an intention-to-treat analysis for the primary analysis. For the primary analysis, we will assess whether access to MAR water reduces the systolic blood pressure (continuous outcome) of the ≥20-year-old participants. Pregnant women will be included in the primary analysis because it is likely few pregnant women will be identified in the 16 communities and separate analysis of pregnant women will be underpowered. We will use generalised linear mixed models with appropriate links for the primary analysis considering random effects for community, households and participants, and fixed effects of steps or visits. We will adjust the effect of MAR systems on blood pressure for age, sex, weight and height, and personal and socioeconomic factors (table 2). We will inspect the missing data patterns and use multiple imputation with chained equations to jointly impute data on missing exposure and confounders to preserve an unbiased association estimate if the data are missing at random conditional on measured variables. We will also conduct subgroup analyses among the households that adhere with the MAR intervention and that exclusively use MAR water. If the trial demonstrates drinking MAR water has health effects, we will investigate the time required for health effects following receiving MAR intervention in secondary analysis.

**Table 2 T2:** Key variables to be used for assessing the health impact of access to MAR water

Outcomes	Exposures	Confounders	Covariates	Moderators
Systolic blood pressure	Access to MAR water	Sex	Age	Drinking/cooking from another water sources
Diastolic blood pressure	Drinking water salinity	Socioeconomic status	Weight	
Pulse pressure	Cooking water salinity	Education	Height	
Mean arterial pressure	Drinking water sources Cooking water sources		Waist circumference	
Urinary total protein Urinary sodium excretion			Mid-upper arm circumference	
			Adding table salt	
			Adding salt for cooking	
			Exercise level	
			Smoking status	
			Use of betel nuts	
			Stress	
			Diet	
			Urinary creatinine	

MAR, managed aquifer recharge.

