### Sample size

The sample size of the stepped-wedge trial was calculated based on the effect of MAR systems to reduce systolic blood pressure of the ≥20-year-old community members. Data from southwest coastal Bangladesh demonstrated a 7 mm Hg lower mean systolic blood pressure among pregnant women who drank pond water compared with those who drank brackish water, and a 17 mm Hg lower mean systolic blood pressure for pregnant women who drank rainwater compared with those who drank brackish water.^35^ The mean reduction in systolic blood pressure following long-term modest salt reduction is 4.2 mm Hg.^50^ For calculations, we considered a mean systolic blood pressure reduction of at least 3 mm Hg among the communities who will have access to MAR water for drinking and cooking purposes compared with those who will use brackish water. The entire population under the MAR community catchment area will be considered as one cluster. Each MAR community serves approximately 300 people, constituting 60–70 households in the catchment area.^28^ The mean household size in southwest coastal Bangladesh is 4.2, approximately 52% of household members are ≥20 years old.^58 59^ Since we will collect blood pressure from all household members ≥20 years old, we estimated an average of 2.2 participants in this age group per household. We will select 28 households per cluster (28×2.2=60 people per cluster). A previously published study in Bangladesh reported SD 13.51 for systolic blood pressure,^60^ but we considered SD 20 for systolic blood pressure to capture a greater variation of blood pressure. We calculated the sample size for the stepped-wedge trial adopting the formula used by Hussey and Hughes.^61^ Although their formula assumed no within-participant correlation over time (cross-sectional design), we applied their formula for a cohort design (same participant followed up over time). The salinity problem and the MAR water quality may be influenced by seasonality over the progression of dry season and participants’ blood pressure may respond differently to different level of sodium exposure in MAR drinking water. Therefore, it is important that we investigate the effect of the MAR system on the same participants over the entire dry season. Since we will investigate the same participants in each step, we will have less participant-level variability and sufficient power compared with a cross-sectional design to investigate the effect of MAR systems. We initially calculated the sample size for a simple unadjusted trial (N_U_), and then multiplied by the design effect for a stepped-wedge trial (DE_SW_). The sample size for a simple unadjusted trial was calculated as 1396 participants (effect size=3, SD of 20 for both groups, 80% power and 5% type I error). The DE_SW_ was 3.04 based on a formula provided by Hussy and Hughes, therefore sample size was 1396×3.04. We also inflated the total sample size considering 10% loss to follow-up. We then followed the approaches of determining the number of clusters required for total sample size considering a fixed cluster size of 60.^62^ We then calculated the number of steps that we need to randomise by dividing the total cluster by steps. We calculated that 16 MAR communities will be required for the study with four communities randomised to access MAR water in each step (figure 3).

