The study has several limitations. We will be unable to control salinity level of drinking water across the 16 MAR communities due to different hydrogeological conditions and volume of infiltrated water across the aquifers. Although the initial electrical conductivity of MAR water will be <2000 μS/cm, electrical conductivity is likely to vary across different MAR communities with the intensification of dry season. Therefore, MAR water salinity will differ across communities at a single point of time, and also for the same community at different points of time. This will result in different versions of exposures (ie, access to MAR water with different salinity levels) that may affect different responses for some participants depending on the version of exposure they will receive.^92 93^ To account this, we will specify the versions of exposure by measuring the salinity level of MAR water available in participants’ households and interpret the response as unit change of salinity at different MAR water salinity levels. As compliance of drinking MAR water may be different across communities despite active encouragement by promoters, one problem of the intention-to-treat analysis is that if the proportions of participants who will always drink MAR water are low compared with those who will not, the potentially greater effect of MAR intervention on blood pressure of fully participating individuals may be washed out by the smaller effect of those who will not comply. To account for this, as a secondary analysis, we will conduct ‘instrumental variable’ (IV) analyses by jointly running two regression models: a regression model for predicting urinary sodium excretion by drinking water salinity, and a regression model for blood pressure prediction given the urinary sodium excretion. The assumption of IV analyses is fulfilled in our context as the exogenous variable (IV) can only affect outcome variable (blood pressure) through influencing the endogenous variable (urinary sodium excretion).^94^ If MAR water has lower salinity than other water sources and if participants always drink MAR water, their urinary sodium excretion will be low compared with those who will not fully participate.

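### If blood pressure varies by community and visit, the primary model's time-constant random effects make the standard error of the MAR effect too small

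*Protocol article*

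**What the plan says.** Under Statistical methods, the Protocol article specifies generalised linear mixed models for the primary intention-to-treat analysis, "considering random effects for community, households and participants, and fixed effects of steps or visits". It names no community-by-visit term, no correlation that decays over time and no robust variance.

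Three other places bear on whether that structure fits:
- Background and rationale describes salinity that rises through the dry season, and people who move from rainwater to pond or saline tube-well water.
- Sample size states that "The salinity problem and the MAR water quality may be influenced by seasonality over the progression of dry season", and that blood pressure may respond differently to different sodium exposure.
- The limitations in the Discussion say that "MAR water salinity will differ across communities at a single point of time, and also for the same community at different points of time". The remedy given there is that "we will specify the versions of exposure by measuring the salinity level of MAR water" found in households, plus a secondary instrumental-variable analysis.

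The article states no ICC, cluster autocorrelation or community-by-visit variance.

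**The concern.** In this design all participants of a community change exposure together, so the information on MAR access lies in 16 × 5 = 80 community-visit cells. The listed random effects imply that two people in a community are equally correlated whether they are measured at the same visit or four months apart. Any local change between visits (a community's own water, weather, work or illness) has no place in that model except the residual, which is estimated from up to 16 × 60 × 5 = 4,800 person-visits. A component that does not average out over the 60 people in a cell is then treated as if it did. The confidence interval becomes too narrow, and a chance pattern of local change could be declared a MAR effect.

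**Working it through.** **The plan's own figures.** Inputs from Sample size: "effect size=3, SD of 20 for both groups, 80% power and 5% type I error"; "The DE_SW_ was 3.04"; "We also inflated the total sample size considering 10% loss to follow-up"; "considering a fixed cluster size of 60".
- Unadjusted size: 2 × (1.960 + 0.842)² × 20² / 3² = 697.7, so 698 per arm and 1,396 in total. This matches.
- Design effect. The article does not print its formula. The usual stepped-wedge form is [1 + ρ(ktn + bn − 1)] / [1 + ρ(ktn/2 + bn − 1)] × 3(1 − ρ) / [2t(k − 1/k)], with k = 4, t = b = 1, n = 60. At ρ = 0.05 it is (15.95 / 9.95) × (2.85 / 7.5) = 0.609. Times 5 visits this is 3.046. The value 3.04 is met at ρ of about 0.03 or 0.055.
- Communities: 1,396 × 3.04 = 4,244 observations; / 0.9 = 4,715; / (60 × 5) = 15.7, so 16. This matches.

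The sample size therefore reproduces. An ICC of about 0.03 to 0.055 is an inference from it, not a stated value.

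**The check.** Layout: 16 communities, 5 visits, 4 communities crossing over at each step, 60 people followed throughout, no attrition. Blood pressure is the sum of a visit effect, the MAR effect, a community effect (variance u), a community-by-visit effect (g), a time-constant person effect (p, with household folded in) and a residual (e). Total variance is 400. ICC = (u + g)/400, cluster autocorrelation = u/(u + g), within-person correlation = p/(p + e). The ICC (0.01 to 0.05), the autocorrelation (0.8 to 1) and the within-person correlation (0.5 to 0.7) are assumptions.

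*One case by hand:* ICC 0.05, autocorrelation 0.9, within-person correlation 0.6.
- u + g = 20, so u = 18 and g = 2 (SD 1.41 mm Hg). p = 0.6 × 380 = 228 and e = 152.
- The visit-specific variance of a community mean is e/60 = 2.53 without the community-by-visit effect, and g + e/60 = 4.53 with it.
- Approximate ratio of true to reported SE: √(4.53 / 2.53) = 1.34.
- Full generalised least squares, letting the residual absorb its small share of g: reported SE 0.65, true SE 0.86, ratio 1.325. Type I error = 2 × [1 − Φ(1.96 / 1.325)] = 13.9%.

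*Type I error of the stated model* (nominal 5%; each range is for within-person correlation 0.5 to 0.7; community-by-visit SD in mm Hg in brackets):

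| ICC | Autocorrelation 1.0 | 0.95 | 0.9 | 0.8 |
|---|---|---|---|---|
| 0.01 | 5.0% [0] | 5.7–6.1% [0.45] | 6.3–7.3% [0.63] | 7.7–9.6% [0.89] |
| 0.02 | 5.0% [0] | 6.4–7.3% [0.63] | 7.7–9.7% [0.89] | 10.5–14.1% [1.26] |
| 0.05 | 5.0% [0] | 8.6–11.1% [1.00] | 12.2–16.7% [1.41] | 18.6–25.6% [2.00] |

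The rates do not depend on the total SD. With the SD of 13.51 that the article also cites, the last cell needs a community-by-visit SD of 1.35 instead of 2.00.

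**Simulation** (REML fits, 1,500 runs per scenario, within-person correlation 0.6). At ICC 0.02 the stated model rejects in 5.0%, 6.7%, 9.2% and 12.7% of runs at autocorrelation 1, 0.95, 0.9 and 0.8. At ICC 0.05 it rejects in 14.9% and 22.3% at 0.9 and 0.8. With a community-by-visit random intercept, the same scenarios give 4.7 to 6.4% with a normal critical value, and 4.5 to 6.2% with t on 59 df (80 cells − 16 communities − 4 visit contrasts − 1).

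**A MAR effect that differs between communities.** In a separate simulation (ICC 0.05, within-person correlation 0.6) there was no local drift, but the MAR effect had mean zero and a between-community SD of 2 mm Hg. The stated model rejected in 12% of runs. The community-by-visit intercept reduced this to 7.8% (normal) or 5.8% (t, 15 df).

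**The case against.** The strongest reply is that nothing in the article shows community-specific drift in blood pressure. The passage on varying MAR salinity concerns water that people drink only after handover. It therefore mainly implies a MAR effect that differs between communities, and if salinity has no effect on blood pressure it adds no community-by-visit variance. Seasonal change that all communities share is absorbed by the visit effects. The larger error rates rest on ICC 0.05. At ICC 0.03, which also fits the design effect, they are about 7–8%, 9–12% and 13–18% at autocorrelation 0.95, 0.9 and 0.8. A community-by-visit SD of 2 mm Hg is two-thirds of the planned 3 mm Hg effect. In the heterogeneous-effect scenario MAR raises blood pressure in about half the communities, which is a weak form of no effect. The stated model is a recognised one, and an analysis plan not shown may add to it.

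Most of this stands, and it makes the finding conditional. It does not remove it:
- The article lists the random effects, so the omission is a stated choice and not silence.
- Local change before handover is plausible, because water sources and salinity shift over the dry season and the pilot found hydrogeological conditions that differ between villages.
- Access can have no effect simply because uptake is low, which the article itself anticipates, while local salinity still moves blood pressure.
- For scale, Background and rationale gives 126.7 − 119.4 = 7.3 mm Hg between the highest and lowest sodium quintiles. Local movement of 1 to 2 mm Hg is not far-fetched, though it is not demonstrated.
- The salinity-specific and instrumental-variable analyses are secondary and leave the primary standard error unchanged.

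**Conclusion.** The point holds as a conditional one. If blood pressure varies by community and visit, the primary model understates the standard error and the 5% test is anti-conservative. Over the assumed ranges, type I error runs from 5% with no such variance to about 26% at ICC 0.05, autocorrelation 0.8 and within-person correlation 0.7. A MAR effect that differs between communities is a separate source of understated error.

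A reader might infer that the false-positive rate is well above 5% as a matter of fact, or that the article says blood pressure drifts differently in each community. The documents support neither. They give no figure for the variance, and they speak of salinity and water sources, not of community-specific drift in blood pressure. This should be fixed before analysis. It does not undermine the design.

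**What to change.** Add a community-by-visit random intercept to the primary model, beside community, household and participant. Test the MAR effect with a small-sample degrees-of-freedom correction suited to 16 communities (Kenward-Roger or Satterthwaite). A community-level random MAR effect can be a pre-specified sensitivity analysis.

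This changes a sentence of the analysis and a little programming; no new data are needed. The price is a wider interval when the variance exists. At ICC 0.05, autocorrelation 0.9 and within-person correlation 0.6, the reported SE goes from about 0.65 to 0.86 mm Hg. In the least favourable scenario for power (ICC 0.05, autocorrelation 0.8, within-person correlation 0.5) the corrected SE is about 1.07. Power for 3 mm Hg is then Φ(3 / 1.07 − 1.96), about 80% with a normal critical value and slightly less with a t value. In the other scenarios power is higher. If the variance turns out to be zero, almost nothing is lost.

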
### Data collection methods

The outcomes of interest will be measured from selected participants of 16 communities irrespective of their access to MAR water during five monthly visits. The interval between two successive blood pressure measurements or two consecutive data collection visits will be at least 4 weeks for each participant. After taking informed written consent from household heads and each participant, research staff will administer a survey using a structured questionnaire to collect information on drinking water sources, household members’ sociodemographic status, medical history, family history of cardiovascular diseases, medication intake, and cardiovascular risk factors including smoking history and alcohol intake during the first monthly visit. Exposure and outcome data will be collected in all five visits. Participants’ weight and hip circumference will be measured in all visits but height will be measured in one visit.

As part of the MAR uptake evaluation, the research staff will collect self-reported data on MAR water use from each household and whether households exclusively or intermittently use MAR water for drinking and cooking during follow-up visits. Research staff will also collect stored drinking and cooking water samples for measurement of electrical conductivity and will ask respondents the source of stored water.

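### The adjustment stated for the intention-to-treat analysis is not limited to pre-access values, so it admits covariates that access to MAR water may itself change

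*Protocol article*

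**What the plan says.** Under Statistical methods the article states: "We will conduct an intention-to-treat analysis for the primary analysis". The question is put in terms of access: "we will assess whether access to MAR water reduces the systolic blood pressure (continuous outcome". The model is a generalised linear mixed model "considering random effects for community, households and participants, and fixed effects of steps or visits". The next sentence reads "We will adjust the effect of MAR systems on blood pressure for age, sex, weight and height, and personal and socioeconomic factors" and refers to Table 2. It is not marked as secondary or as a sensitivity analysis.

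The Covariates column of Table 2 holds age, weight, height, waist and mid-upper arm circumference, added table salt, "Adding salt for cooking", exercise, smoking, betel nut use, stress, diet and "Urinary creatinine". Sex, socioeconomic status and education are listed as confounders. The table serves every outcome, including the two urinary ones, and does not assign covariates to models.

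On timing, Data collection methods says "weight and hip circumference will be measured in all visits", while height is taken once. Biomarker measurements has urine, the source of creatinine, collected at each household visit. The questionnaire on sociodemographic status, medical history and cardiovascular risk factors belongs to the first visit. No timing is given for added salt, diet or stress. Study design says that no community has MAR water at the first step.

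**The concern.** An intention-to-treat effect of access is the whole effect, by whatever route it acts. A covariate measured after access starts may be one of those routes. Lower sodium intake could change body weight. Promoters also encourage cooking with MAR water, so the salt added in the pot may change when the water becomes less salty. Holding such a variable fixed removes the part of the effect that runs through it. If the variable shares unmeasured causes with blood pressure, conditioning on it can also create an association that is not causal.

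At stake is what the primary estimate means. With post-access covariates it would answer what access does with weight or salt habits held constant, whereas the stated objective asks whether access lowers blood pressure. Such a bias does not shrink with more participants. The timing of access is randomised, so these covariates are not needed to control confounding of the access effect.

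**Working it through.** **1. The plan's own figures.** These reproduce, so sample size is not the issue. Per group: 2 × (1.96 + 0.8416)² × 20² / 3² = 2 × 7.849 × 400 / 9 = 697.7, rounded up to 698, or 1396 in total, as stated. Taking the stated design effect of 3.04 and reading the product as observations over five visits: 1396 × 3.04 = 4243.84; divided by 0.9 for loss to follow-up, 4715.4; divided by 60 × 5 = 300 per community, 15.7, rounded up to 16 communities.

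**2. Which covariates meet both conditions for bias?** The value must be measured after access begins, and access must plausibly change it.

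| Covariate | Tied to the systolic model? | Documented after access? | Could access change it? |
|---|---|---|---|
| Weight | Yes, named in the adjustment sentence | Yes, all visits | Plausibly |
| Added table or cooking salt, diet | Through Table 2 | Timing not stated | Plausibly, cooking salt above all |
| Stress | Through Table 2 | Timing not stated | Unclear |
| Urinary creatinine | Unclear; may serve the urinary outcomes only | Yes, urine at each visit | Possibly |
| Waist circumference | Through Table 2 | Not documented; the repeated measure named is hip | Unclear |
| Age, sex, height, education, socioeconomic status | Yes | Not relevant | No |

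Weight is the firm case and cooking salt the next most plausible.

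**3. Size, given assumed inputs.** Let *a* be the change in the covariate caused by access and *b* its coefficient in the fitted model. Then

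adjusted effect = total effect − *a* × *b*.

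The document gives neither *a* nor *b*. Everything below is illustrative, with a total effect of −3 mm Hg.

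- Weight, *a* = −0.5 kg, *b* = 1 mm Hg/kg: −3 + 0.5 = −2.5. Hidden: 0.5/3 = 17%.
- Compensating added salt, *a* = +1 g/day, *b* = 0.5 to 1 mm Hg/g: −3.5 to −4.0. Overstated by 0.5 to 1 mm Hg, or 17% to 33%.
- *a* = 0, or visit-1 values used: no difference.

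**4. Simulation check.** Setting: 16 communities of 60, five visits, true total effect −3 mm Hg, participant and visit effects removed (a within-person estimator in place of the full mixed model), 60 runs per row. Differences are taken from the rounded means.

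| Weight change (kg) | Slope (mm Hg/kg) | Unadjusted | Adjusted for visit weight | Difference | −*a* × *b* |
|---|---|---|---|---|---|
| 0 | 1 | −3.05 | −3.06 | −0.01 | 0 |
| −0.5 | 1 | −3.10 | −2.63 | +0.47 | +0.5 |
| −1 | 1 | −2.93 | −1.91 | +1.02 | +1 |
| −0.5 | 0.5 | −3.08 | −2.82 | +0.26 | +0.25 |
| +0.5 | 1 | −2.89 | −3.37 | −0.48 | −0.5 |

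The departures of the unadjusted column from −3 (at most 0.11) are simulation noise. Both estimates come from the same simulated data, and their difference follows the formula.

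**5. Power, if part of the effect is adjusted away.** With 80% power at 3 mm Hg and the standard error unchanged, power = Φ(*d*/3 × 2.8016 − 1.96). If an adjusted variable carries 10%, 20% or 30% of the effect, *d* is 2.7, 2.4 or 2.1 mm Hg, and power is about 71%, 61% or 50%.

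**The case against.** The strongest reply is that the article nowhere says visit-level values enter the model. Measuring weight at all visits describes data collection, and covariate timing is something a condensed article may leave to a fuller document. That would dispose of a complaint about silence alone. Here, however, the article does fix an adjustment set, names weight in it, records weight after access begins and attaches it to an analysis labelled intention-to-treat. Followed literally with the repeated data, that text permits a primary model that no longer estimates the total effect.

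A reader might infer that the primary result will certainly not be an intention-to-treat effect, or that every Table 2 covariate goes into the systolic model. The documents support neither. The table covers all outcomes and several exposures, and the sentence calls on it for personal and socioeconomic factors. Creatinine has a documented use elsewhere, as the denominator of the urinary ratios in Table 1. Salt, diet and stress may be first-visit items, in which case adjusting for them is harmless. Waist circumference is not documented as repeated. Urinary sodium, the main step on the causal pathway, is listed as an outcome and kept out of the covariates, which suggests that the authors had the pathway in mind.

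It is also fair to object that the magnitudes rest wholly on assumed inputs, and that zero is among the possible values.

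**Conclusion.** The concern holds conditionally. As written, the adjustment for the primary analysis admits variables that access can change and places no pre-access restriction on them. The estimate departs from the total effect of access only if post-access values are used and access changes them; otherwise the bias is zero. Neither direction nor size can be derived from the document. Under the assumed inputs tried here the discrepancy runs from 0 to about 1 mm Hg in either direction, against a 3 mm Hg target. The defect is that the text allows both a valid and a biased primary model, and the choice between them could be made after the data are seen.

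**What to change.** State under Statistical methods that the primary systolic blood pressure model contains access, step and the community, household and participant random effects, plus only fixed characteristics and visit-1 values: age, sex, height, education, socioeconomic status, visit-1 weight, and visit-1 added salt, diet or stress if these are collected then. Mark in Table 2 which covariate belongs to which analysis and at which visit it is taken. Keep urinary creatinine for the urinary outcomes. Use post-access weight, salt, diet and stress only in secondary or pathway analyses labelled as such.

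The cost is one sentence and a table edit. Weight is already measured at visit 1, before any community has access, so no new data are needed for it. The one possible downside is a small loss of precision from leaving out visit-level covariates.
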